##### Secondary study parameters

All the secondary outcomes will be presented as frequencies with percentages for dichotomous outcomes, means with standard deviations for continuous normally distributed variables and medians with interquartile ranges for non-normally distributed variables.

We plan to calculate the differences within groups between baseline and 12 months using either a paired t-test, Wilcoxon signed rank test or McNemar test for PFIQ, PFDI-20, PISQ-IR, the compound measure, vaginal pH, vaginal atrophy (objective and subjective outcomes), adverse events, gynecological interventions performed, costs and compliance. Differences between groups (including relative risks with 95% confidence interval) will be analyzed using one-sample t-test for normally distributed numerical data, Mann–Whitney U tests for not normally distributed numerical data, chi-square testing for categorical data and Fisher’s exact testing for rare outcomes.

The secondary outcome quality of life at 1 year after the procedure, will be measured with the EQ-5D-5L and will be analyzed using the utility calculation that was used in other studies [51]. Quality of life outcomes will be described and analyzed accordingly. Difference in utilities between groups will be estimated using a linear regression. For each time point, QALYs will be calculated by multiplying the utilities by time (as fraction of a year) [52, 53]. Results will be further incorporated in the cost-effectiveness analyses.

Adherence to therapy will be assessed by comparing tube weights to the anticipated weight if used according to protocol. Participants will also keep a perioperative diary on the use of vaginal cream to calculate adherence to therapy until 6 weeks postoperative. Moreover, adherence to therapy will be calculated at 6 and 12 months postoperative from the adherence questionnaire.

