### Outcome measures

The primary outcome is subjective improvement of POP symptoms at 1 year follow-up; the percentage of women with much or very much improvement of POP symptoms, measured with the Patient Global Impression of Improvement (PGI-I) scale [42]. PGI-I is a 7-point Likert scale, with scores ranging from very much worse to very much improved. Success is defined as ‘much or very much’ improvement.

Secondary outcomes are surgical success, POP-Q anatomy in all compartments, surgery related complications, general quality of life, disease specific quality of life (micturition and defecation), sexual function, signs and complaints of vaginal atrophy, vaginal pH, adverse events, costs, and adherence to treatment. Surgical success is defined as the absence of POP beyond the hymen (POP-Q at gynecological examination), the absence of bulge symptoms (absence of bulge symptoms is defined as a negative response to the question, “Do you see or feel a bulge in the vaginal area”), and absence of reoperation or additional pessary therapy for POP [43]. Follow up is scheduled at 6 weeks, 6 months and 12 months postoperative. Data will be collected using validated questionnaires (See also ‘Data collection’ and Fig. 1) and out-patient visits including gynecological examination are performed by an independent gynecologist.

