### Randomization

Women will be randomized in a 1:1 ratio to perioperative treatment with estriol or perioperative treatment with placebo using computer-generated randomly permuted blocks of sizes 4, 6 and 8. Blinded randomization will be performed by the participating center using online software (Castor Electronic Data Capture, Amsterdam, the Netherlands [online] available at: http://castoredc.com). The central coordinating pharmacy of the Academic Medical Center Amsterdam receives an automatically generated email containing the allocated treatment for each randomized patient from the Castor system. After also receiving a doctor’s prescription, the pharmacy will deliver study medication at the participant’s home address by courier service.

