#### Hospital visits

The participant will visit the hospital prior to starting with the study medication, 6 weeks postoperative and 12 months postoperative. History and gynecological examination including POP-Q, vaginal pH and assessment of vaginal atrophy will be performed. To reduce interviewer bias, the POP-Q measurement at 12 months postoperative will be done by an independent examiner—instead of the surgeon. Unscheduled visits and phone calls are also recorded in respect to additional costs.

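### Secondary outcomes get within-arm baseline-to-12-month tests, some with no baseline to pair, while the between-arm tests take no baseline value and name a one-sample t-test

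*Protocol article*

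**What the plan says.** All of the analysis wording is in the protocol article, Secondary study parameters. The first step is within each arm: "We plan to calculate the differences within groups between baseline and 12 months using either a paired t-test", with the Wilcoxon signed rank and McNemar tests as alternatives. The list of outcomes for this step starts with PFIQ, PFDI-20, PISQ-IR, the compound measure, vaginal pH and vaginal atrophy, and ends with "adverse events, gynecological interventions performed, costs and compliance".

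The next sentence plans between-arm tests: "Differences between groups (including relative risks with 95% confidence interval) will be analyzed using one-sample t-test for normally distributed numerical data". It adds Mann–Whitney, chi-square and Fisher's exact tests for other kinds of data. For EQ-5D utilities there is a separate line: "Difference in utilities between groups will be estimated using a linear regression". Its covariates are not stated.

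Hospital visits fixes when baseline is: "The participant will visit the hospital prior to starting with the study medication, 6 weeks postoperative and 12 months postoperative". Outcome measures defines surgical success, the likely meaning of the compound measure, and one of its components is "absence of reoperation or additional pessary therapy for POP".

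**The concern.** There are three problems in two consecutive sentences.

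- A paired test needs a value before treatment and a value after it. Several listed outcomes exist only after treatment starts, so the prescribed test cannot be run on them.
- Where a pair does exist, change within one arm combines the prolapse operation, the passage of time and any effect of the cream. Both arms have the operation. A within-arm p value therefore does not address the question that randomization was set up to answer. Two such p values side by side also invite the reading that estriol worked because its arm crossed p < 0.05 and the placebo arm did not.
- The between-arm tests should carry the inference, but they leave the baseline measurement unused. For normally distributed data, the test named is not a two-group test.

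The outcomes concerned include PFDI-20, which Economic evaluation makes the primary effect measure of the cost-effectiveness analysis, the trial's stated aim.

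**Working it through.** **Inputs.** Sample size gives 150 women per arm with 10% expected loss, so 150 × 0.90 = 135 per arm at 12 months. Alpha is 0.05 (taken as two-sided) and power 80%. The correlation r between baseline and 12-month values is not in the document. It is an assumption here, shown as a range.

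**1. The plan's own figure.** The only sample size given is for the primary outcome (80% versus 65%). With unpooled variance, n = (1.960 + 0.842)² × (0.80 × 0.20 + 0.65 × 0.35) / 0.15² = 7.849 × 0.3875 / 0.0225 = 135.2, so 136 per arm, as stated. No figure is given for the secondary outcomes.

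**2. Can each listed outcome be paired?** Baseline comes before the cream and before surgery.

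| Outcome | Pre-treatment value? |
|---|---|
| Compliance | No. Tube weights, the diary and the adherence questionnaire all refer to use of the cream |
| Adverse events | No, they arise during the trial |
| Gynecological interventions performed | No, they are counted after entry |
| Costs | Unclear. iMCQ and iPCQ are listed, but their schedule is in Fig. 1, which is not shown |
| Compound measure | If it is surgical success, two components (prolapse beyond the hymen, bulge symptoms) can be assessed before surgery; reoperation cannot |
| Vaginal pH, atrophy | Yes, examined at the first visit |
| PFDI-20, PFIQ-7, PISQ-IR | Yes, as the planned paired tests presuppose |

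**3. What within-arm p values show when the arms do not differ.** In units of the outcome's SD, the standard error of mean change is √(2(1 − r)/n). With r = 0.5 and n = 135 it is √(1/135) = 0.0861. Within-arm power is p = Φ(shift/0.0861 − 1.96). The chance that exactly one arm is significant is 2p(1 − p).

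| Common change (SD) | p | Both significant | Exactly one significant |
|---|---|---|---|
| 0.1 | 0.212 | 4.5% | 33% |
| 0.2 | 0.642 | 41% | 46% |
| 0.3 | 0.937 | 88% | 12% |
| 0.5 | 0.9999 | 99.99% | 0.01% |

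The last column cannot exceed 50%, reached at p = 0.5. A large common change makes both arms significant and says nothing about estriol. A small one often produces a contrast between arms that is not there.

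**4. What the unused baseline is worth.** Relative variance of the between-arm difference is 1 for 12-month values, 2(1 − r) for change scores and 1 − r² for ANCOVA. The detectable difference at 80% power is 2.802 × √(2/135 × relative variance).

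| r (assumed) | ANCOVA variance | Reduction against 12-month values | Equivalent sample size | Detectable difference: 12-month values → ANCOVA |
|---|---|---|---|---|
| 0.3 | 0.91 | 9% | 1/0.91 = 1.10 | 0.341 → 0.325 SD |
| 0.6 | 0.64 | 36% | 1/0.64 = 1.56 | 0.341 → 0.273 SD |

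The article does not say whether 12-month values or changes are compared. Against change scores the variance ratio is 0.91/1.40 = 0.65 at r = 0.3 and 0.64/0.80 = 0.80 at r = 0.6, so ANCOVA is also the more precise choice there.

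**5. The t-test.** A one-sample t-test compares one mean with a fixed value. Two independent randomized arms need a two-sample test. This is probably a slip, but as written normal numerical outcomes have no usable between-arm test.

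**The case against.** A reader might infer that the within-arm tests replace a comparison of the arms. They do not: the very next sentence plans between-arm tests with relative risks and confidence intervals, utilities are compared by regression, and the primary outcome is compared between arms by relative risk and chi-squared test. The within-arm tests come in addition.

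A reader might also infer that the between-arm tests are biased because they ignore baseline. The documents do not support that. The protocol article states: "Women will be randomized in a 1:1 ratio to perioperative treatment with estriol or perioperative treatment with placebo". Under that design an unadjusted comparison is valid and only less efficient. Choice of covariates is often left to an analysis plan, which is not shown here. What remains is that the article itself names specific tests for these outcomes, and none of them takes a covariate. The confounders mentioned under Data analysis are illustrated by withdrawal and missing data, not by baseline values.

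A discordance near 50% should not be taken as a forecast. It is a ceiling, and it falls close to zero if surgery shifts a symptom scale by 0.5 SD or more, which may well happen. That defence has a price: in that case the within-arm tests carry no information about the cream.

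Finally, a missing baseline is certain only for adverse events, interventions performed and compliance. For costs and the compound measure it is possible, not shown. ANCOVA would also not suit categorical measures such as a graded atrophy assessment.

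**Conclusion.** The point holds in this form. Paired tests are prescribed for at least three outcomes that have no pre-treatment value. For the outcomes that do have one, within-arm p values do not estimate the effect of estriol. The between-arm tests named take no baseline value, and the one for normal data cannot compare two arms.

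The 9% to 36% reduction in variance rests on two assumptions: a correlation of 0.3 to 0.6, and a comparison of 12-month values. It is a gain in precision and in protection from chance imbalance, not the repair of a bias. Only secondary outcomes are affected, though they include the effect measure of the cost-effectiveness analysis. The wording should be changed; it does not threaten the primary result.

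**What to change.** Amend Secondary study parameters, and the analysis plan if there is one, before unblinding:

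- Drop the within-arm significance tests. Keep within-arm change as descriptive rows.
- For numerical outcomes measured at baseline (PFDI-20, PFIQ-7, PISQ-IR, vaginal pH, numerical atrophy scores), make the between-arm difference at 12 months with 95% CI, from ANCOVA on arm and baseline value, the analysis. For categorical ones, use a suitable baseline-adjusted or direct between-arm comparison.
- State whether baseline utility is a covariate in the utility regression.
- Compare adverse events, interventions performed, compliance and any other outcome without a baseline directly between arms.
- Define the compound measure, and say whether costs have a baseline value.
- Replace the one-sample t-test by an independent two-sample t-test wherever an unadjusted comparison remains.

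The cost is wording only. The baseline data are already being collected, and no extra women, visits or questionnaires are needed.

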#### Questionnaires and diary

Participants will be asked to complete online questionnaires, generated in Castor EDC (when preferred, it is possible to complete the questionnaires on paper). Participants will receive 2 or more of the following questionnaires at baseline and 6 weeks, 6 months and 12 months postoperative (See also Fig. 1):Questionnaire on baseline characteristics and medical history (including age, length, weight, parity, education, history of diabetes, respiratory diseases and smoking, family history of POP).Patient Global Impression of Improvement (PGI-I): to assess subjective improvement of POP symptoms [42].EuroQoL (EQ-5D-5L): a general quality of life questionnaire, to evaluate health utilities and the corresponding quality adjusted life years (QALYs) [45].Pelvic Floor Disability Index-20 (PFDI-20): to measure symptom distress on disease specific quality of life, focusing on POP, urinary incontinence, and fecal incontinence [46].Pelvic Floor Impact Questionnaire-7 (PFIQ-7): to measure impact on specific quality of life, focusing on POP, urinary incontinence, and fecal incontinence [46].Most Bothersome Symptom questionnaire: to assess the most bothersome urogenital symptoms [47].The Pelvic organ prolapse Incontinence Sexual Questionnaire-IR (PISQ-IR): a condition-specific measure of sexual function in women with pelvic floor dysfunction, including urinary and anal incontinence and pelvic organ prolapse [48].Medical Consumption Questionnaire (iMCQ): for cost effectiveness analysis [49].Productivity Cost Questionnaire (iPCQ) to assess productivity loss [50].Adherence questionnaire: on adherence to treatment, experience using perioperative vaginal cream and influencing factors on compliance. This questionnaire has been developed for this study and is provided as Additional file 1.Adherence diary: a perioperative diary will be kept on the use of vaginal cream, from start till 6 weeks postoperative. Adverse reactions associated with vaginally administered estriol cream (e.g. temporary itch or irritation of the application site) can be reported in the diary as well.Adherence to treatment: Study medication will be delivered at the participant’s home address at two time points; 2 tubes at randomization and 3 tubes at 5 months post-randomization. Participants are asked to return the study medication at 5 months post-randomization and at the end of the study—12 months post-operative. In order to asses adherence to treatment, tubes will be weighted on a scale (Denver Instrument Company, TR-602, digit: 0.01 g) and recorded in Castor EDC.

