### Statistical analysis

#### Sample size

The sample size is based on the primary endpoint of subjective cure rate (PGI-I) at 12 months postoperative. A difference in subjective cure of more than 15% is considered clinically relevant. Assuming a subjective cure of 80% in the intervention group and a subjective cure of 65% in the control group; 136 women in each trial arm are needed to assess superiority of the intervention, with a power of 80% and an α of 0.05. With an expected 10% loss to follow up, a number of 150 women will be included in each trial arm (total sample size 300 women).

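### For PFDI-20, PFIQ-7 and PISQ-IR the stated tests give 6-week and 6-month scores no role, so women without a 12-month form drop out of the 12-month arm comparison

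*Protocol article*

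**What the plan says.** The Questionnaires and diary section states: "Participants will receive 2 or more of the following questionnaires at baseline and 6 weeks, 6 months and 12 months postoperative". Which instrument is given at which visit is shown only in Fig. 1, whose content was not available for this check.

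The Secondary study parameters section plans to "calculate the differences within groups between baseline and 12 months" by paired t-test, Wilcoxon signed rank or McNemar test. Its list of outcomes includes PFIQ, PFDI-20 and PISQ-IR. The next sentence covers differences between groups: a t-test (the article writes one-sample), Mann–Whitney, chi-square or Fisher's exact test. It gives no time point. No repeated-measures model is named. The Data analysis section says that withdrawal and missing data will be considered, without a method.

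The Economic evaluation section makes PFDI-20 the primary effect measure and assesses the primary endpoint at 12 months after surgery. The Sample size section plans for loss: "With an expected 10% loss to follow up, a number of 150 women will be included in each trial arm".

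**The concern.** Each named test needs one value, or one baseline-and-follow-up pair, per woman. If the arm comparison is made at 12 months, a woman without a 12-month form cannot enter it, whatever she reported at 6 weeks or 6 months.

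Lost numbers matter less here than selection. Women doing badly at 6 months may leave at different rates in the two arms. The women who remain at 12 months are then no longer comparable, although the score that explains the loss may be in the database. Adjusting a 12-month comparison for baseline does not cure this, because the same women are still missing. PFDI-20 is the effect side of the main cost-effectiveness ratio, so a bias in its 12-month difference passes straight into the trial's headline economic result.

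**Working it through.** **Step 1. The plan's own figures.** Inputs from the Sample size section: 80% versus 65%, "with a power of 80% and an α of 0.05". With two-sided α and unpooled variance:

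n = (1.960 + 0.842)² × (0.80 × 0.20 + 0.65 × 0.35) / 0.15² = 7.849 × 0.3875 / 0.0225 = 135.2, so 136 per arm.

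This matches the article. The pooled formula gives 138. Enrolment is 136 × 1.1 = 149.6, so 150 per arm. With 10% lost, 150 × 0.9 = 135 per arm have 12-month data and 15 do not.

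**Step 2. Assumptions not in the documents.** Scores have unit SD. Correlations are 0.4 (baseline with each later visit), 0.6 (6 weeks with 6 months), 0.55 (6 weeks with 12 months) and 0.7 (6 with 12 months). The true 12-month difference is −0.35 SD. About 10% of 12-month forms are missing, and those women have both earlier forms.

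**Step 3. Random dropout: standard error of the 12-month difference.**

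- 12-month scores alone: √(2/135) = 0.122.
- Change from baseline: √(2 × 2 × (1 − 0.4)/135) = 0.133.
- Baseline-adjusted 12-month score: √(2 × (1 − 0.4²)/135) = 0.112.
- All postoperative visits, no baseline term. The share of 12-month variance explained by 6 weeks and 6 months is (0.55² + 0.7² − 2 × 0.6 × 0.55 × 0.7)/(1 − 0.6²) = 0.516. SE = √(2 × (0.484/135 + 0.516/150)) = 0.119.
- All postoperative visits with baseline. The 12-month variance given baseline is 0.84, of which 0.366 is explained by the earlier visits. SE = √(2 × (0.474/135 + 0.366/150)) = 0.109.

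All of these are unbiased here. The gain of 0.109 over 0.112 is about 2%. Without the baseline term, the all-visit model is about 6% less precise than simple baseline adjustment (0.119 against 0.112).

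Over a wider set of assumed correlations (0.3 to 0.8, equal or decaying with time), the mixed model has the information of about 136 to 142 women per arm against 135 complete cases at 10% missing. At 20% missing it is about 122 to 134 against 120.

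**Step 4. Selective dropout: mean estimates from 4,000 simulated trials per scenario (truth −0.35).**

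| Dropout | 12-month only | Change score | Baseline-adjusted | All visits |
|---|---|---|---|---|
| Poor 6-month score, placebo arm only | −0.287 | −0.322 | −0.301 | −0.349 |
| Opposite directions in the two arms | −0.221 | −0.293 | −0.249 | −0.348 |

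Shortfall, 12-month only: 0.063/0.35 = 18% and 0.129/0.35 = 37%. Change score: 0.028/0.35 = 8% and 0.057/0.35 = 16%. Baseline-adjusted: 0.049/0.35 = 14% and 0.101/0.35 = 29%.

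**Step 5. How strong a selection this implies.** If dropouts lie d SD from their arm's 6-month mean, the bias per affected arm is roughly r × d × 0.1/0.9. Here r = 0.7 for the 12-month score, 0.7 − 0.4 = 0.3 for the change score and 0.7 − 0.4² = 0.54 for the baseline-adjusted score. Setting 0.7 × d/9 = 0.063 gives d = 0.81. The formula then gives 0.3 × 0.81/9 = 0.027 and 0.54 × 0.81/9 = 0.049, close to the simulated 0.028 and 0.049. The bias is proportional to d: at d = 0.4 the one-arm shortfall in the 12-month comparison is 0.7 × 0.4/9 = 0.031, or 9%.

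**The case against.** Several points on the other side stand.

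- **The quoted sentence concerns change within groups.** The between-group sentence names no time point, so confining the arm comparison to 12 months is an inference. It is a fair one: the sentence follows directly on the baseline-to-12-month window, and the Economic evaluation section sets the endpoint at 12 months.
- **A reader might infer that every questionnaire ignores the intermediate visits.** The article does not say so. Adherence is calculated at 6 and 12 months, and the Secondary study parameters section computes QALYs at each time point.
- **A reader might also infer that 6-week and 6-month PFDI-20 or PFIQ-7 scores certainly exist.** The text says only that two or more instruments are sent across the visits. Fig. 1 decides it.
- **The bias figures follow from the assumptions.** Dropout was made to depend on an observed 6-month score, the condition under which a likelihood model is unbiased. Dropouts must lie about 0.8 SD from their arm's mean, and nothing in the article suggests opposite-direction dropout in a double-blind placebo trial. The one-arm bias in the 12-month comparison is about half a standard error (0.063 against 0.122).
- **An article may leave the missing-data method to an analysis plan.** That is right, and the absence of an imputation method is not the point here. What is questioned is the window and tests that the article does state.

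**Conclusion.** The point holds for PFDI-20, PFIQ-7 and PISQ-IR as a cheap improvement to a stated method. By the named tests, intermediate scores have no role. About 15 women per arm would leave a 12-month comparison and the PFDI-20 effect in the cost-effectiveness ratio.

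The case rests on protection against selective dropout. The 8% to 37% range illustrates what could happen under the assumed correlations and dropout patterns; it does not forecast bias in this trial. Precision alone would hardly justify the change.

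A reader might conclude that the trial's main result is at risk. The documents do not support that: PGI-I at 12 months is analysed under its own section, and neither it nor adherence is covered by this point.

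The article is also inconsistent on EQ-5D. The Secondary study parameters section uses each time point for QALYs, while the Economic evaluation section takes utilities from baseline and 12 months.

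**What to change.** For each numerical questionnaire score that Fig. 1 schedules at more than one postoperative visit, specify one linear mixed model:

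- Outcome: the score at all postoperative visits.
- Terms: arm, visit, arm-by-visit, baseline score and baseline-by-visit, with an unstructured covariance. The baseline term is needed for the 0.109 standard error above.
- Population: every randomised woman with at least one postoperative value.
- Report: the 12-month between-arm difference with its 95% confidence interval.

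Use the PFDI-20 estimate in the economic evaluation, refitting the model within each of the planned 1000 bootstrap replicates. Reconcile the two sections on which EQ-5D time points feed the QALYs.

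The cost is wording in the analysis plan, to be settled before unblinding; no new data are needed. The downside is reliance on a missing-at-random assumption. That is weaker than what the stated tests need, but it gives no protection if dropout depends on 12-month status not foreshadowed by earlier scores.

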#### Data analysis

Both an intention-to-treat analysis and per protocol analysis will be performed to evaluate the effect of perioperative estrogen; taking possible confounders in consideration such as study withdrawal and missing data. Analyses will be done using SPSS version 26.0. A *p* value of < 0.05 is considered a threshold for significance. Baseline characteristics will be presented using descriptive statistics, with frequencies (numbers, mean or median with respectively percentages, standard deviation or quartiles).

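### The plan names a one-sample t-test for comparing the two arms on normally distributed secondary outcomes; that test cannot compare two arms, and an independent-samples t-test was probably meant

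*Protocol article*

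**What the plan says.** Under Secondary study parameters the protocol article treats two kinds of comparison in consecutive sentences.

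- **Within arms:** "We plan to calculate the differences within groups between baseline and 12 months using either a paired t-test, Wilcoxon signed rank test or McNemar test"; the outcomes covered include PFIQ, PFDI-20, PISQ-IR and vaginal pH.
- **Between arms:** the next sentence opens with "Differences between groups (including relative risks with 95% confidence interval" and says that these differences "will be analyzed using one-sample t-test for normally distributed numerical data". For the remaining data types it names "Mann–Whitney U tests for not normally distributed numerical data", chi-square tests for categorical data and Fisher's exact test for rare outcomes.

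Women are allocated 1:1 to estriol or placebo (Randomization). The significance rule, under Data analysis, is that a p "value of < 0.05 is considered a threshold for significance"; it does not say whether tests are one- or two-sided. The primary outcome has its own chi-squared test (Primary study parameter), and EQ-5D utilities are compared by linear regression (Secondary study parameters).

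**The concern.** A one-sample t-test asks whether the mean of one sample differs from a number fixed in advance. Comparing estriol with placebo involves two independent samples, and both means carry sampling error. The named test has no place for the second arm's error, and the article supplies no fixed number to test against.

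The sentence governs the between-arm test for every numerical secondary outcome that takes the normal-data route. The patient-reported scales PFDI-20, PFIQ-7 and PISQ-IR may be among them, and vaginal pH as well. If the words were followed literally, the p values and confidence intervals for those outcomes would not be valid comparisons of the arms. If the test is silently replaced at analysis, the reported method departs from the published plan without explanation.

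**Working it through.** **1. Can another part of the article make the wording right?**

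- *Change from baseline.* A one-sample test of change against zero is the paired t-test. The preceding sentence already assigns that test to within-arm change, so the between-arm sentence cannot mean it.
- *Comparison with a benchmark.* This would need a reference value, and none is given for any of these outcomes.
- *Companion tests.* Mann–Whitney U, chi-square and Fisher's exact test all compare independent groups. The parametric counterpart of Mann–Whitney U is the independent-samples t-test.
- *Correction elsewhere.* There is none. The chi-squared test for the primary outcome and the regression for utilities concern other endpoints.

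The name is therefore wrong for its stated purpose, and the context shows what was probably intended.

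**2. Arm sizes for the calculation.** The Sample size section assumes 80% against 65% and states that "136 women in each trial arm are needed to assess superiority of the intervention, with a power of 80% and an α of 0.05". Two-sided, with unpooled variances:

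n = (1.960 + 0.842)² × (0.80 × 0.20 + 0.65 × 0.35) / 0.15² = 7.85 × 0.3875 / 0.0225 ≈ 135.2, rounded up to 136.

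The stated figure is reproduced. It belongs to the primary outcome and does not depend on the t-test; it is used here only to set n. The planned enrolment of 150 per arm is the other value used.

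**3. Type I error under one literal use.** Suppose the other arm's observed mean is entered as the constant. The statistic is then

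T = (x̄₁ − x̄₂) / (s₁/√n).

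With no true difference, equal n and equal SDs, the numerator has standard error σ√(2/n), while the test uses an estimate of σ/√n. T is thus distributed as √2 times a t variable with n − 1 degrees of freedom. At a nominal two-sided 0.05 (sidedness assumed):

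- Large samples: 2 × (1 − Φ(1.96/√2)) = 2 × (1 − Φ(1.386)) = 16.6%.
- Exact, P(|t(n−1)| > t₀.₉₇₅/√2): 16.4% at 136 per arm and 16.4% at 150 per arm.
- Simulation, 200,000 trials at each size: 16.4% (136) and 16.5% (150).

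**4. Range under assumptions that the article does not give** (large-sample formulas):

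| Assumption | Formula | Type I error |
|---|---|---|
| Reference-arm SD 0.8 times the tested arm's | 2(1 − Φ(1.96/√(1 + 0.8²))) | 12.6% |
| Reference-arm SD 1.25 times the tested arm's | 2(1 − Φ(1.96/√(1 + 1.25²))) | 22.1% |
| 120 women in the tested arm, 150 in the reference arm | 2(1 − Φ(1.96/√(1 + 120/150))) | 14.4% |
| 150 women in the tested arm, 120 in the reference arm | 2(1 − Φ(1.96/√(1 + 150/120))) | 19.1% |

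**5. With the test corrected.** In the same simulations the independent two-sample t-test rejects in 4.9% of trials at 136 per arm and 5.0% at 150 per arm, which is the nominal level.

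**The case against.** The best defence is that this is a slip of naming and that nobody plans an invalid analysis. The neighbouring tests point to the independent-samples t-test, and software asked for a one-sample test would demand a constant that the plan does not supply, so an analyst would probably notice. That stands as an account of what was meant, and it lowers the weight of the point. It does not make the sentence right: a prespecified method should be executable as written, and this one is not.

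Two stronger readings are tempting, and the article supports neither.

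- A reader might infer that the trial will test these outcomes with a false-positive rate near 17%. That needs one arm's observed mean to be entered as the fixed value, which the article nowhere says. Under the likely reading the rate is the nominal 5%.
- A reader might infer that every secondary result, or the trial's main conclusion, is compromised. The primary outcome uses a chi-squared test, EQ-5D utilities use linear regression, and dichotomous outcomes such as surgical success use chi-square or Fisher's exact test. The economic evaluation estimates uncertainty by bootstrap, even though PFDI-20 is its main effect measure. Any numerical outcome judged non-normal goes to Mann–Whitney U. Which scales will take the normal-data route cannot be known from the article.

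**Conclusion.** The point holds as an error in a stated analysis rule, limited to between-arm tests of numerical secondary outcomes judged normally distributed. The named test cannot make the comparison it is assigned, and nothing else in the article corrects it.

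The size is conditional. If the rule were applied literally with the other arm's mean as the constant, the type I error would be about 16% instead of 5%, given two-sided testing, equal arms and equal SDs. The range is about 13% to 22% for assumed SD ratios of 0.8 to 1.25. If an independent-samples test is used, as was probably intended, there is no inflation. The wording should be corrected before unblinding, but it does not put the primary conclusion or the sample size in doubt.

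**What to change.** In the between-arm sentence under Secondary study parameters, replace the one-sample t-test with an independent two-sample t-test, and state that the between-arm mean difference will be reported with its 95% CI. The Welch form is a reasonable choice because it does not assume equal variances, but either form of the two-sample test cures the error. If a statistical analysis plan repeats the wording, change it there too.

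Optionally, for outcomes also measured at baseline, the comparison could come from a linear model of the 12-month value on arm and baseline value. That is a gain in precision and is not needed to correct the mistake; an unadjusted comparison of randomised arms is valid.

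The cost is one line of text. No new data, extra participants or change to the conduct of the trial is needed.
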